### TCM syndrome differentiation criteria

According to the TCM theory, *QZQG* formula is suitable for severe influenza that meets the pattern of Plague Simultaneously Involving Weifen and Qifen (*PSIWF* pattern). The TCM differentiation criteria for *PSIWF* pattern include symptoms, signs for the tongue, and signs for the pulse. The symptoms include at least high fever, cough, sticky phlegm, thirsty, sore throat, and red eyes. The signs for the tongue are red tongue and thick yellow or greasy tongue. The signs for the pulse are slippery or rapid pulse. To meet the criteria of TCM syndrome differentiation, participants should have all symptoms of *PSIWF* pattern as well as the TCM signs for the tongue and pulse.

### Informed consent {26a}

A doctor will confirm if the patients satisfy the criteria after consent being given. Subsequently, the medical officers of the trial team in every center will communicate with the patients and their families to inform the possible benefits and risks of participating in this study. Patients will be given sufficient time to fully consider trial entry and to ask questions of investigators. Patients willing to participate in this trial need to sign a written informed consent form. A consent for clinical biological specimens will also be obtained to specifically address the collection of biological specimens for future use including serum, plasma, urine, and fecal specimens.

### Interventions

#### Explanation for the choice of comparators {6b}

The active arm is orally administered *QZQG* formula in addition to routine supportive care, in which oseltamivir is the only antiviral allowed. *QZQG* formula has been used in treating exogenous febrile disease (acute upper or lower respiratory tract infection) in China for hundreds of years. *Jiuweiqianghuo* granule has been recommended by the guideline for the diagnosis and treatment of influenza in China [6]. There are safety and efficacy data for *QZQG* formula in individuals with respiratory tract infection [21, 22]. The dose of *QZQG* was selected on long-term clinical application experience in China. The control arm is placebo in addition to routine supportive care.

#### Intervention description {11a}

*The intervention is described as follows for the experimental and control groups:*

The *QZQG* group will receive two bags of *QZQG* formula granules (4.6 g/per bag), twice a day, 30 min after eating for 7 days. Whole ingredients of *QZQG* formula include *Rhizoma seu Radix Notopterygii* (*Qiang Huo*) 18g, *Gypsum Fibrosum* (*Sheng Shi Gao*) 25g, *Codonopsis Radix* (*Dang Shen*) 7.5g, *Angelicae Dahuricae Radix* (*Bai Zhi*) 18g, *Saposhnikovia Divaricata* (*Fang Feng*) 18g, *Rhizoma Atractylodis* (*Fu Chao Cang Zhu*) 18g, *Pinellia Ternata* (*Ban Xia*) 9g, *Taraxacum* (*Pu Gong Ying*) 15g, *Astragalus Membranaceus* (*Huang Qi*) 15g, *Lophatherum Gracile *(*Dan Zhu Ye*) 3g, *Radix Ophiopogonis* (*Mai Dong*) 15g, *Rehmannia Glutinosa* (*Sheng Di Huang*) 12g, *Scutellaria baicalensis* (*Huang Qin*) 12g, *Asari Radix Rhizoma* (*Xi Xin*) 3 g, *Ligusticum wallichii* (*Chuan Xiong*) 12g, *Honey-fried Herba Ephedrae*(*Zhi Ma Huang*) 6g, *Vitex negundo*(*Huang Jing Zi*) 20g and *Clycyrrhizae Radix Et Rhizoma* (*Gan Cao*) 12g. *QZQG* formula granules and placebo granules are manufactured and provided by Sichuan New Green Pharmaceutical Technology Development Co., Ltd. The Chinese herbal medicine placebo with the same weight as the test drugs consists of 20-fold dilution of 4.60 g of *QZQG* formula granules and maltodextrin with the addition of artificial pigment and flavoring agents.

The placebo group will receive placebo granules and used the same medication as the test group. Placebo is identical to the test drug in appearance, smell, and taste. This preparation of placebo has been frequently used in herbal medicine trials in China. All drugs are hidden in a uniform package with the same label, and each package contains a 7-day dose. Both test drugs and placebo will be packaged and labeled by School of Public Health, Fudan University, according to the random number table and drug blinds.

#### Criteria for discontinuing or modifying allocated interventions {11b}

Use of study drug will be halted or modified if any of the following criteria develop:
Severe gastrointestinal symptoms prevented oral administration of the trial drug.Respiratory compromise: dyspnea, wheezing, stridor, hypoxemia.A decrease in systolic blood pressure to < 90 mmHg or > 30% decrease from baseline or a diastolic drop of > 30% from baseline.Tachycardia with an increase in resting heart rate to > 130 bpm; or bradycardia < 40 that is associated with dizziness, nausea, or feeling faint.Syncope.Confusion.Any other symptom or sign which, in the investigators’ judgment, requires withdrawal of the subject from the study warrants halting the oral administration.

#### Strategies to improve adherence to interventions {11c}

All participants are inpatients and receive the whole process management of the research doctor, which will significantly improve the compliance. In every site, an independent drug administrator is responsible for dispensing, reclaiming, storing, and recording of all test drugs. The research nurses in each center will be responsible for the distribution of drugs and placebo and fill in the drug management diary. The subjects will complete the medication under the direct supervision of nurses.

#### Relevant concomitant care permitted or prohibited during the trial {11d}

Considering ethical requirements of IRB, all enrolled patients need to receive one oseltamivir capsule (75 mg/per capsule), twice a day for 7 days [6]. Since patients with severe influenza in the all centers of China are hospitalized, the necessary intravenous fluid therapy is allowed. When the body temperature of a participant rises to higher than 39.0 °C, physical cooling and antipyretics are allowed to be used to reduce the fever. The treatments for hypertension, diabetes, cerebral infarction, and other underlying diseases are allowed as well. The doctors of the trial team must carefully record the name, dose, usage, and duration of the concomitant drugs or treatment in the case report form (CRF).

However, no other antivirals for influenza are allowed during the study period. Adjunctive therapies such as corticosteroids were prohibited. In addition, it is absolutely forbidden to take other Chinese herbal medicines and Chinese patent medicine during the study period or within 14 days before randomization. When the patients have drug-related adverse events or serious complications such as viral pneumonia, hepatoprotective drug, antibacterials, and other necessary treatments are completely allowed and recorded.

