#### Inclusion criteria

*The inclusion criteria are as follows:*
Diagnosis of influenza A and/or B by a positive Rapid Influenza Diagnostic Test (RIDT) or reverse transcriptase-polymerase chain reaction (RT-PCR).• Positive results from local tests are acceptable if conducted within the 24 h prior to screening.• A patient with a negative RIDT may be enrolled if influenza is suspected based on local surveillance data or if the patient reports contact with a known case of influenza within the prior 7 days and all other inclusion criteria are met.Granting of written informed consent.Male or female aged 18 to 65 years at the time of signing informed consent form.Ability to comply with the study protocol, in the investigator’s judgment.Participants who require hospitalization for severe influenza or acquire influenza during hospitalization, the severity of which requires an extension of hospitalization.Participants will require at least one of the following objective criteria of severe influenza: (i) duration with axillary temperature over 39 °C ≥ 3 days, accompanied by severe cough, sputum, blood sputum, or chest pain; (ii) rapid respiratory rate (≥30 times per minute), difficulty breathing and cyanosis of lips; (iii) arterial oxygen saturation (SaO2)/ pulse oxygen saturation (SPO2) ≤94% in room air condition; (iv) requires ventilation or supplemental oxygen to support respiration; (v) with only one complication related to influenza (e.g., pneumonia, central nervous system involvement, myositis, rhabdomyolysis, acute exacerbation of chronic kidney disease, asthma or chronic obstructive pulmonary disease (COPD), severe dehydration, myocarditis, pericarditis, exacerbation of ischemic heart disease).The time interval between the onset of symptoms and randomization is within 96 h. The onset of symptoms is defined as either time of the first increase in body temperature (≥ 38 °C) or time when the patient experiences at least one general or respiratory symptom.Conforming to the standard of TCM syndrome differentiation.

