#### Exclusion criteria

*The exclusion criteria are as follows:*
Participants hospitalized for exclusively social reasons (e.g., lack of caregivers at home).Participants expected to be discharged within 48 h, according to the investigator’s judgment.Participants weighing < 40 kg.Participants who have received more than 48 h of antiviral treatment for the current influenza infection prior to screening.Participants with known severe renal impairment or receiving continuous renal replacement therapy, hemodialysis, peritoneal dialysis.Participants with any of the following laboratory abnormalities detected within 24 h prior to or during screening (according to local laboratory reference ranges:• Alanine transaminase (ALT) or aspartate transaminase (AST) level > 5 times the upper limit of normal (ULN).• ALT or AST > 3 times the ULN and total bilirubin level > 2 times the ULN.Any serious medical condition or abnormality in clinical laboratory tests that, in the investigator’s judgment, precludes the participant’s safe participation in and completion of the study.With mental changes or convulsions (e.g., slow response, drowsiness and restlessness).With severe gastrointestinal symptoms (e.g., severe nausea, vomiting, diarrhea and even dehydration).With one of the following critical illnesses: respiratory failure, acute necrotic encephalopathy, septic shock, multiple organ dysfunction, or other serious clinical conditions requiring intensive care.With tuberculosis, measles, AIDS, or other infectious diseases.Women who are pregnant (including a positive pregnancy test at enrollment), breastfeeding, or within 2 weeks post-partum.Known history of allergy or severe intolerance of oseltamivir and herbal medicines, as determined by the investigator.Currently or have been involved in another anti-influenza treatment trial in the last 28 days.Patients who have been treated with oral Chinese medicine within 4 weeks.Patients who, in the opinion of the investigator, would be unlikely to comply with required study visits, self-assessments, and interventions.

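### The corticosteroid ban in section {11d} has no stated exception, yet patients can be enrolled because of an acute asthma or COPD exacerbation, and the protocol does not say which rule prevails

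*Protocol article*

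**What the plan says.** Inclusion criteria: "Participants will require at least one of the following objective criteria of severe influenza". Five criteria follow, (i) to (v). Criterion (v) is met by a single complication of influenza, and its examples include "acute exacerbation of chronic kidney disease, asthma or chronic obstructive pulmonary disease (COPD), severe dehydration".

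Exclusion criteria: there is no exclusion for asthma or COPD exacerbation as such. Such a patient is excluded if critically ill, the listed conditions being "respiratory failure, acute necrotic encephalopathy, septic shock, multiple organ dysfunction, or other serious clinical conditions requiring intensive care", or if the investigator judges that a serious condition makes participation unsafe.

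Section {11d} contains three statements that bear on steroids, in this order:

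- A permission: "The treatments for hypertension, diabetes, cerebral infarction, and other underlying diseases are allowed as well".
- In the next paragraph, which opens with a word of contrast, the ban: "Adjunctive therapies such as corticosteroids were prohibited". It stands between a ban on other influenza antivirals and a ban on other Chinese medicines.
- A closing permission. Its trigger is "When the patients have drug-related adverse events or serious complications such as viral pneumonia", and in that case "hepatoprotective drug, antibacterials, and other necessary treatments are completely allowed and recorded".

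Section {20a} lists COPD and asthma among the underlying diseases to be used as covariates. Section {20b} plans a subgroup analysis by chronic respiratory disease.

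**The concern.** The trial opens an entry route for patients whose qualifying complication is an airway exacerbation, and then states a rule that, taken literally, bars corticosteroids for them. If corticosteroids are usual treatment for such an exacerbation, a clinician who follows the sentence as written would withhold them from a patient enrolled because of that exacerbation. The same clinician might also stop a patient's maintenance steroids.

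What is at stake is patient safety and uniform background care. The rule has to be applied at the bedside in several centers (seven hospitals are named under Study setting {9}, ten centers are given under Recruitment {15}), and the text supports more than one reading.

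**Working it through.** There is no stated figure to reproduce and no arithmetic beyond a count. The check sets the provisions side by side.

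**Step 1. Can such a patient be enrolled?** The Inclusion criteria list 5 severity criteria and require at least 1. An acute asthma or COPD exacerbation meets (v), so it suffices for the severity requirement. The remaining inclusion criteria still apply.

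**Step 2. Do the exclusions remove them?** Only in part. Respiratory failure and other conditions needing intensive care are excluded, and the investigator may exclude on safety grounds. The exacerbations that remain are mainly those short of critical illness.

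**Step 3. Are such patients expected?** Yes. Besides criterion (v), COPD and asthma are planned covariates in {20a}, and chronic respiratory disease defines a subgroup in {20b}. The note to Table 1 provides an oxygen-saturation scale for hypercapnic COPD. That is weaker support, because it is a general scoring instruction.

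**Step 4. Does section {11d} settle whether they may have steroids?**

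| Provision in {11d} | Reading that permits steroids | Why it does not settle the matter |
|---|---|---|
| Treatment of underlying diseases allowed | {20a} counts COPD and asthma as underlying diseases, so their treatment is covered | The ban comes afterwards, in a paragraph introduced as a contrast; and under (v) an exacerbation is classed as a complication of influenza, not only as background disease |
| Ban on adjunctive therapies such as corticosteroids | *Adjunctive* means steroids added to treat influenza | This meaning is not stated; and a complication of influenza sits on the border of it |
| Necessary treatment of serious complications allowed | An exacerbation is a complication, and the treatment is necessary | *Serious* is not defined, and an exacerbation is not named; a non-serious exacerbation and maintenance treatment fall outside the wording |

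Each permissive reading is reasonable. None is stated, and no order of precedence is given.

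**Step 5. Do other sections settle it?** No. Section {11b} ("Use of study drug will be halted or modified if any of the following criteria develop") governs the study drug, not concomitant steroids. The rule for worsening patients under Assessment of adverse events starts a separate treatment regimen, but only once a participant is judged critically ill.

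**Step 6. What remains exposed?** Serious complications and critical illness can be treated under {11d} and the adverse-event section. The uncertainty therefore falls mainly on exacerbations not judged serious and on maintenance steroids. For maintenance treatment the underlying-disease permission is the stronger argument, so the exposure there is smaller.

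**Step 7. How many patients?** This cannot be derived. The document gives no expected share with asthma or COPD and no expected steroid use.

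**The case against.** The strongest reply is that the protocol, read as a whole, already allows these steroids. The ban sits between two rules whose evident purpose is to keep rival influenza treatments out of an adjuvant trial, so *adjunctive* most naturally means steroids given for influenza. Treatment of underlying diseases is expressly allowed, and {20a} places COPD and asthma among them. The closing sentence of {11d} gives viral pneumonia as its example of a serious complication, and pneumonia appears in the same (v) list as the airway exacerbations. A site could therefore treat an exacerbation as equally covered. The article is also condensed, staff are trained before the trial starts, and the clinical premise about steroids comes from outside the document.

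Much of this stands. It rules out the reading, which the ban sentence invites when taken alone, that steroids are forbidden without exception: the same section contains permissions that can be read as exceptions. The permissive reading may well be what the sponsor intends.

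It does not remove the point. The text states a ban and a colliding entry route, so this is more than detail left to a longer document. The reader must infer which rule yields, and the inference is least secure for an exacerbation that nobody would call serious. Training may bring sites into line, but the article does not say what they are taught on this.

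A reader might also infer that steroid-treated patients would be lost from the per-protocol set, or that the treatment comparison would be biased. The document supports neither inference. Section {20c} excludes for a major protocol violation but does not class prohibited medication as one. With blinding and randomization stratified by center, differences in steroid practice between sites would not systematically favor one arm.

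**Conclusion.** The point holds as an unresolved conflict between a stated ban and a stated entry route. It does not hold as an absolute prohibition. A site applying the ban literally could withhold steroids for a non-serious asthma or COPD exacerbation or stop maintenance steroids, while another site gives them under the neighboring permissions.

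The conclusion rests on one assumption from general practice, that corticosteroids are usual treatment in these situations. Its size cannot be given in patients, and no effect on power, bias or any analysis set is claimed. It is a minor point and a cheap improvement, justified by patient safety and consistency of care.

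**What to change.** In {11d}, limit the ban to corticosteroids given to treat influenza itself. Add that corticosteroids for an asthma or COPD exacerbation, or as maintenance treatment of an underlying disease, are permitted and recorded in the CRF. Report their use by arm in one descriptive table.

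The cost is a sentence and a table. No new data are needed, because {11d} already requires concomitant treatment to be recorded and Table 2 schedules this from screening to day 28. The downside is slightly more variation in background treatment. If the sponsor does intend a total ban, the change belongs in criterion (v) instead: asthma and COPD exacerbations should then no longer be a route into the trial.

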### Outcomes measurements {12}

#### Primary outcome measure

The primary outcome is proportion of clinical improvement within 7 days. And clinical improvement is defined as at least one of the following criteria: (i) 3 points or less in the 7-category ordinal scale; (ii) National Early Warning Score 2 (NEWS2) of ≤2 and maintained for 24 h [23]. Seven-category ordinal scale was used in other influenza study [24–27]. The seven-category ordinal scale consisted of the following categories: 1, not hospitalized with resumption of normal activities; 2, not hospitalized, but unable to resume normal activities; 3, hospitalized, not requiring supplemental oxygen; 4, hospitalized, requiring supplemental oxygen; 5, hospitalized, requiring nasal high-flow oxygen therapy, noninvasive mechanical ventilation, or both; 6, hospitalized, requiring ECMO, invasive mechanical ventilation, or both; and 7, death. The UK’s National Early Warning Score 2 have good predictive abilities in patients with infections and sepsis [23], which are detailed in the Table 1.

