**Table 1 Tab1:**
[figure not shown]
National Early Warning Score 2 (NEWS2)

NEWS2: (i) The oxygen saturation should be scored according to either the SpO2 Scale 1 or 2 presented in the table above. The SpO2 Scale 2 is for patients with a target oxygen saturation requirement of 88–92% (e.g., in patients with hypercapnic respiratory failure related to advanced lung diseases, such as chronic obstructive pulmonary disease [COPD]). This should only be used in patients confirmed to have hypercapnic respiratory failure by blood gas analysis on either a prior or their current hospital admission. The decision to use the SpO2 Scale 2 should be made by the treating physician and should be recorded in the eCRF. In all other circumstances, the SpO2 Scale 1 should be used. (ii) For physiological parameter “Air or Oxygen?”: Any patients requiring the use of oxygen or other forms of ventilation to maintain oxygen saturations and support respiration should be assigned a score of 2. (iii) The consciousness level should be recorded according to the best clinical condition of the patient during the assessment. Patients who are assessed as “Alert” (A) should be assigned a score of 0. Patients assessed as “New Confusion” (C), “Responsive to Voice” (V), “Responsive to Pain” (P), or “Unconscious” should be assigned a score of 3

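### The NEWS2 arm of the primary endpoint adds only patients still on oxygen or ventilation, so a patient escalated to high-flow oxygen or noninvasive ventilation can be counted as clinically improved

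*Protocol article*

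**What the plan says.** The protocol article, under Primary outcome measure, states that "clinical improvement is defined as at least one of the following criteria". The first is "i) 3 points or less in the 7-category ordinal scale" and the second is "ii) National Early Warning Score 2 (NEWS2) of ≤2 and maintained for 24 h". The abstract repeats the either/or rule, without the 24 h condition.

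The same section defines the categories on either side of the cut. The highest category that meets the first criterion is "3, hospitalized, not requiring supplemental oxygen". Category 4 is an inpatient on ordinary oxygen. The next step up is "5, hospitalized, requiring nasal high-flow oxygen therapy, noninvasive mechanical ventilation, or both". Category 6 is an inpatient on invasive ventilation or ECMO. Categories 1 and 2 are patients out of hospital, and category 7 is death.

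Note (ii) under Table 1 says that those "requiring the use of oxygen or other forms of ventilation to maintain oxygen saturations and support respiration should be assigned a score of 2". Note (iii) gives an alert patient 0 points for consciousness and any lower level 3 points.

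**The concern.** The two criteria are alternatives, but they treat respiratory support differently. The ordinal scale separates ordinary oxygen (category 4) from high-flow oxygen or noninvasive ventilation (category 5) and from invasive ventilation or ECMO (category 6). NEWS2, as scored here, gives all three the same 2 points, and 2 is also the threshold for success.

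Neither criterion refers to the patient's state at randomization. The two halves of the endpoint can therefore disagree about one patient: worse on the ordinal scale, improved on NEWS2. The either/or rule settles the disagreement as a success. This endpoint carries the sample size and the only confirmatory comparison, so it should be clear that a responder has not moved to a higher level of support.

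**Working it through.** The plan has no figure of its own on this point to reproduce. The check is an enumeration of the definition.

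**Inputs.** Criterion (i), criterion (ii) and the category definitions come from Primary outcome measure. The oxygen and consciousness points come from the notes under Table 1. The body of Table 1 is not available in the text reviewed. I assume only that item scores are non-negative, that they add up, and that 0 is attainable on each remaining item.

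**Formula.** NEWS2 = (2 if on any oxygen or ventilation, otherwise 0) + points on all other items. Criterion (ii) requires this sum to be 2 or less.

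| Ordinal category | Meets (i)? | Oxygen item | Other points allowed under (ii) | Added by (ii) alone? |
|---|---|---|---|---|
| 1–3 | yes | not needed | not needed | no, already counted |
| 4 | no | 2 | 2 − 2 = 0 | yes, if all other items are 0 |
| 5 | no | 2 | 2 − 2 = 0 | yes, if all other items are 0 |
| 6 | no | 2 | 2 − 2 = 0 | in principle only |
| 7 | no | – | – | no |

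The patients who meet (ii) but not (i) are therefore exactly those in categories 4 to 6 with NEWS2 = 2 + 0 = 2 for 24 h. This does not depend on whether the 24 h condition also applies to (i).

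**Example.** A patient is randomized in category 4. On day 2 the patient is moved to high-flow oxygen (category 5). From day 4 the patient is alert, with 0 on every other item, for 24 h. NEWS2 is 2 + 0 = 2, criterion (ii) is met, and the patient is a responder. The ordinal category has gone from 4 to 5.

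**Does another rule intercept this patient?**
- Section {11b} halts or modifies study drug for respiratory compromise.
- The Harms section stops study drug and requires a report within 24 h when a patient becomes critically ill.
- The allocation section allows emergency unblinding on deterioration and says that such a patient is excluded.
- The analysis population section {20c} sets no outcome for escalation.

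None of these makes the patient a non-responder. Stopping drug is not an outcome rule, and exclusion after unblinding is not non-response.

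**How wide is the route?** Every item apart from oxygen must be 0 for 24 h within the 7 days. That is realistic for an alert patient settled on high-flow oxygen or noninvasive ventilation. It is unlikely on invasive ventilation or ECMO, where any consciousness level below alert adds 3 points and takes the total to at least 5.

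**A related route through (i).** Entry through prolonged fever or a single complication does not require oxygen. Such a patient can start in category 3, meet (i) at once, escalate later in the 7 days and still count. Amending (ii) alone would not close this route.

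**The case against.** The best defence is that the composite is deliberate. The Discussion argues that a single endpoint may misjudge the drug and cites earlier use of the two scales in severe influenza. Criterion (ii) also has a legitimate purpose: a category 4 patient who is alert, with normal findings on everything but oxygen for 24 h, may well have improved from a high score. The route to the anomaly is narrow, and entry excludes respiratory failure and conditions needing intensive care. Deterioration also appears elsewhere, in time on oxygen, length of stay, complications, adverse events and the 24 h reporting of critically ill patients.

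All of this limits the importance of the point. It does not remove it. A reason for combining the scales is not a reason to count a rise from category 4 to 5 as improvement, and none of the listed secondary outcomes grades the level of support.

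Two stronger readings are tempting, and the document supports neither.

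- *A reader might infer that the 20-point planned difference is diluted by a calculable amount.* That would require 50% and 70% to be the rates under (i) alone. The sample size section ties the 50% rate and the 20-point increase to the primary endpoint, which is the composite, so they already include whatever (ii) contributes. No share of patients qualifying through (ii) alone is given. Any such share would also include stable category 4 patients, who should remain responders.
- *A reader might infer that the endpoint hides harm.* That would need more escalation in the QZQG arm to pass through this route than in the placebo arm, and nothing in the article suggests this. Equal shares of the remaining patients in both arms would only attenuate a difference.

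**Conclusion.** The point holds as a defect of definition. As written, criterion (ii) adds only patients on oxygen or ventilation whose NEWS2 is exactly 2. Because that score does not grade support, a patient who moves from category 4 to category 5 and is stable for 24 h is classed as clinically improved. No other rule in the article reverses this.

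Its size is unknown. The route is narrow and the article gives no frequency, so no loss of effect or power should be attached to it. The conclusion rests on the wording of the endpoint, the notes under Table 1, and the assumption that all remaining NEWS2 items can score 0 on support. How often that happens on high-flow oxygen or noninvasive ventilation is a matter of judgement.

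**What to change.** 1. Amend criterion (ii) to: *NEWS2 of 2 or less maintained for 24 h, with the patient in ordinal category 4 or lower and not in a higher category than at randomization throughout those 24 h.*
2. Add: *A patient whose ordinal category rises above baseline and has not returned by day 7 is not a responder under either criterion.* This also covers a patient who enters in category 3, meets (i) at once and then escalates without returning.
3. Report, by arm, the number of responders who qualify through (ii) alone.

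Stable category 4 patients can still respond through (ii), so the purpose of the composite is kept. The change does not address patients who enter in category 3 and simply stay there. They still meet (i), which is a separate matter.

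Cost: a slightly lower response rate in both arms, and recording of the ordinal category (level of support) at each daily assessment on days 1 to 7. The data collection section names both scales, but Table 2 as printed lists no ordinal-scale or support-level item, so the schedule and case report form should be checked and extended if needed. The wording should be settled before unblinding.
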